## Abstract

**Background:**

Degenerative lumbar spondylolisthesis (DLS), one of the most common causes of low back pain, is defined as the displacement of a vertebral body over the lower vertebral body with degenerative changes and the absence of fracture or defect in the vertebral ring. This disease is a common and frequently occurring disease. Currently, there are many clinical treatment methods, but there is no specific method, and most of them have the characteristics of slow effect and easy recurrence.

**Objective:**

The objective of this study is to summarize and analyze the effects of treatment of degenerative lumbar spondylolisthesis by Tongdu Bushen acupuncture, intradermal acupuncture, and moxibustion integrated therapy combined with core muscle training program (CMT) on the improvement of pain degree and dysfunction index, as well as the gait characteristics.

**Methods:**

120 patients with DLS will be recruited and randomly divided into two groups using electroacupuncture combined with the CMT group as the control group. Visual Analogue Scale (VAS), Oswestry Disability Index (ODI), and Japanese Orthopedic Association score (JOA) will be used for evaluation. The spatiotemporal and kinematics parameters in gait analysis, as well as the ability of lumbar muscle contraction, fatigue resistance, relaxation, and coordination of lumbar muscle in surface electromyography (sEMG), will be used as objective observation indexes to observe the effectiveness of Tongdu Bushen acupuncture, intradermal acupuncture, and moxibustion integrated therapy combined with CMT. *Discussion*. Tongdu Bushen acupuncture, intradermal acupuncture, and moxibustion integrated therapy is a traditional Chinese medicine treatment for DLS. Our results will provide evidence to determine whether the integrated therapy can effectively treat DLS, as well as its advantages and safety, and lay a foundation for further research. This trial is registered with ChiCTR2100050409.

## 1. Introduction

Degenerative lumbar spondylolisthesis (DLS), one of the most common causes of low back pain, is defined as the displacement of a vertebral body over the lower vertebral body with degenerative changes and the absence of fracture or defect in the vertebral ring. DLS often occurs at the level of L4. It will cause intervertebral foramen stenosis, compression of nerve roots, and sciatica in severe cases [1]. Studies have shown that the incidence rate of DLS is between 19.1% and 43.1%, with an average age of 71.5 to 75.7 years old, and women are more frequent than men. However, the incidence rate of this disease varies from the crowd and the type of measurement [2].

Although the pathophysiology of the disease has a clearer understanding and there are many clinical treatment methods for DLS, the optimal treatment for this disease is still controversial. For patients with severe DLS, most of them choose the surgical intervention of single decompression or fusion decompression [3] if they have acute spinal cord compression symptoms such as intestinal/bladder dysfunction. Mild DLS patients will choose conservative treatments generally [4], such as activity restriction, the use of anti-inflammatory drugs and epidural steroid injections for pain relief, and other physical rehabilitation exercises [5–8]. For example, exercise therapy is widely recognized as an effective treatment for pain caused by spondylolisthesis [9]. However, due to the lack of prospective studies, the best conservative treatment mode has not been clarified, and most of them have problems such as slow efficacy and easy recurrence.

Studies have shown that acupuncture is an effective way to treat diseases of the lumbar spine [10]. The Tongdu Bushen acupuncture, intradermal acupuncture, and moxibustion integrated therapy is a traditional Chinese medicine therapy for DLS. In addition, the effect of core muscle training program (CMT) on trunk-pelvis kinematics during DLS and healthy gait [11], it also helps to improve the clinical symptoms of patients with DLS. Studies have shown that core stabilization increases the range of motion in the lumbar spine and reduces pain and dysfunction [12]. Compared with conventional physical therapy, the incidence of disability was significantly reduced in patients who received CMT [13]. In order to judge the effectiveness of Tongdu Bushen acupuncture, intradermal acupuncture, and moxibustion integrated therapy combined with CMT in the treatment of DLS, we started this study with electroacupuncture (EA) combined with CMT as the control group. This study is a randomized controlled study. We hypothesized that the method of the experimental group is a more effective method for DLS.

## 2. Materials and Methods

### 2.1. Study Design

This study was designed as a randomized controlled study. Once a treatment has been established as an effective method, it would be unethical to undertake placebo-controlled trials [14], which has led to more widespread application of clinical noninferiority trials over recent decades [15, 16]. A noninferiority trial design could be a better alternative to indirectly show the efficacy of a new treatment [17]. The purpose of this study was to summarize and analyze the effects of treatment of degenerative lumbar spondylolisthesis by Tongdu Bushen acupuncture, intradermal acupuncture, and moxibustion integrated therapy combined with CMT on the improvement of pain degree and dysfunction index, as well as the gait characteristics. Therefore, this study will investigate the efficacy of the experimental group and the control group in the treatment of DLS. In this study, 120 patients with DLS I° who met the criteria of this study will be recruited and randomly divided into the experimental group and the control group, with 60 patients in each group. All subjects will receive a complete written explanation of the study protocol and informed consent. The study flow chart is shown in Figure 1.

### 2.2. Inclusion Criteria

The inclusion criteria are as follows:Meeting the diagnostic criteria for DLS (I° and posterior spondylolisthesis)Adults (50 years ≤ aged ≤75 years) with DLSHaving persistent symptoms for less than 24  months before enrollmentPatients who had not taken psychotropic drugs before enrollmentPatients who had not received traditional Chinese and western medicine for DLS in the first 2 monthsThere were no pathological features that had influence on the results of this study, such as the history of severe lumbar trauma, tuberculosis, tumor, fracture, moderate and severe osteoporosis or above, and other lumbar bone destructionBeing willing to give informed consent and cooperate with the subjects of the study

### 2.3. Exclusion Criteria

The exclusion criteria are as follows:Adults (aged ≥75 years or aged ≤50 years) with DLSSpinal cord compression or obvious nerve root injury with low back pain and severe sensorimotor abnormalities of lower limbsDLS with severe blood diseases, hypertension, diabetes, and endocrine system diseasesDLS with mental disorders or patients who cannot cooperate with the testPrevious lumbar surgery historyDLS with severe infection, tumor, osteoporosis, fracture, structural deformity, nerve root syndrome, cauda equina syndrome, and other diagnosed definite pathological changesPatients who took combination medication or participated in other trials during treatment

### 2.4. Sample Size Calculation

This is a randomized controlled trial design, and the primary outcome was that patients' lower back pain improved. Our early clinical observation with a small sample (10 cases) found that 10 days of the experimental group and the control group can reduce scores on the JOA scale by 3.41 ± 1.86 and 2.24 ± 1.67 points, respectively. When the significance test level is set to 0.05 and the test power is set to 0.9, the sample size is calculated as follows:(1)$$\begin{array}{c} N=2\times {\left[\frac{\left(Z_{\alpha /2}+Z_{\beta }\right)\times \sigma }{\delta }\right]}^{2}. \end{array}$$When *α* is 0.05 and *β* = 0.1, the normal distribution quantile table shows the following:(2)$$\begin{array}{c} Z_{\alpha /2}=1.96,\\ Z_{\beta }=1.282, \end{array}$$where *σ* and *δ* represent the population standard deviation and allowable error, which are 1.86 and 1.17, respectively. The result is 54 by plugging these data into the formula, so 54 patients will be needed in each group. Since there may be a 10% dropout rate, we will recruit 60 participants in each group for this study.

### 2.5. Participants

The study will be conducted at the First Affiliated Hospital of Henan University of Traditional Chinese Medicine (TCM). These DLS patients who meet the inclusion criteria and the exclusion criteria will be recruited through the rehabilitation outpatient or inpatient department of the hospital, the WeChat public account of the rehabilitation center, and the brochure. Recruitment began in June 2021 and is scheduled to end in December 2022.

### 2.6. Randomization

All included participants will be randomly assigned to the experimental group and the control group at a ratio of 1 : 1. This study will be randomized to generate a sequence of random numbers using randomization software, and a specialized statistician who is not a searcher in this study will be responsible for processing the results. Meanwhile, sequentially numbered and sealed opaque envelopes which reveal random numbers will be provided to the patients according to the order of the subjects' visits (the order of visits was consistent with the envelope number), and these envelopes will be hidden until informed consent is obtained.

### 2.7. Blinding

Due to the limitations of acupuncture treatment, the acupuncturists cannot be blinded to who will be informed of the grouping of participants before treatment. The outcome evaluators and data statisticians will be blinded to the group allocation to improve the quality of this study as much as possible. In addition, participants will be assigned to different rooms during the treatment to avoid exchange from each other. Therapists, data managers, and statisticians are not allowed to communicate with others about the treatment of patients.

### 2.8. Interventions

During the following treatment period, all eligible patients will be treated in the assigned groups. The patients in the experimental group will be treated with Tongdu Bushen acupuncture, intradermal acupuncture, and moxibustion integrated therapy, as well as CMT, while patients in the control group will receive EA and CMT. The two groups were assigned their own treatment regimens, treatment once a day, 10 times as a session, for 2 sessions over 3 weeks. (The locations are specifically presented in Table 1). The treatment will be conducted in the Rehabilitation Center of the First Affiliated Hospital of Henan University of Chinese Medicine by professional acupuncturists.

#### 2.8.1. Tongdu Bushen Acupuncture

The traditional chinese medicine believes that kidney essence deficiency and Du Yang indolence are the internal cause of spinal disease. Tongdu Bushen acupuncture mainly involves dredging governor's arteries, promoting blood circulation and collcollars, tonifying liver and kidney, and nourishing qi. The acupoints will include bilateral Shenshu (BL23), Jiaji (EX-B2), Yaoyangguan (GV3), Mingmen (GV4), Yaoshu (GV2), Ashi point (the point where the patient feels most pain), and affected side Huantiao (GB30), Chengshan (BL57), and Weizhong (BL40). First, the skin will be disinfected, and then, single-use acupuncture needles (0.25 ^*∗*^ 40 mm, Hwato, Suzhou, China) will be inserted into acupoints. Acupuncturists will manually stimulate the needles to achieve Deqi. Subsequently, Shenshu (BL23), Mingmen (GV4), Yayangguan (GV3), and Ashi point will be getting moxibustion after acupuncture, and the other acupuncture sites will be irradiated by TDP. The needles will be left for 30 min.

#### 2.8.2. Intradermal Acupuncture

The acupoints will include Ashi point (the point where the patient feels most pain) and bilateral Shenshu (BL23), Yaoyangguan (GV3), Zhibian (BL54), Fengshi (GB31), Yanglingquan (GB34). First, the skin will be disinfected, and then, the intradermal acupuncture is secured to the skin with tape. The needles will be left for 24 h.

#### 2.8.3. Moxibustion

Moxibustion will be carried out along the first lateral line of the bladder meridian. Drugs of moxibustion will include clove, cinnamon, making aconite, asarum, Weilingxian, transbone grass, 120g in total. During the procedure, the patient was placed in the prone position, the back was exposed, and the skin was routinely disinfected with 75% ethanol. Break ginger and filter off part of the ginger juice, stir it evenly with the above powder, and make a rectangular medicine cake about 15 cm wide and 4 cm thick, and lay it flat on the above moxibustion site. Aged fine moxa was selected to make a three-sided moxa pillar with a bottom width of about 5 cm and a height of about 3 cm and placed on the cake and lit moxa. When moxibustion burned at a height of 2/3, the ash was removed, and moxibustion was continued with moxibustion added with moxibustion for 3 times. To the degree that the patient feels warm but can tolerate, the skin at the moxibustion site is slightly flushed after moxibustion, pay attention to prevent scalding, remove the medicine cake and moxa ash after moxibustion, and wipe the back clean with a hot damp towel.

#### 2.8.4. Electropuncture (EA)

The acupoints will include bilateral Yaoyangguan (GV3), Mingmen (GV4), Yaoshu (GV2), and affected side Huantiao (GB30), Chengshan (BL57), Weizhong (BL40). First, the skin will be disinfected, and then, single-use acupuncture needles (0.25 ^*∗*^ 40 mm, Hwato, Suzhou, China) will be inserted into acupoints. Acupuncturists will manually stimulate the needles to achieve Deqi. After feeling of Deqi (the sensations including soreness, numbness, distention, or heaviness), it was connected to the EA device (G6805-2A, Shanghai Huayi Medical Instrument Co., Ltd., China, dense waves 20 times/second, frequency 2.5 Hz). The treatment will be left for 30 min.

#### 2.8.5. Core Muscle Training Program (CMT)

Muscles, such as the multifidus, gluteus medius, transverse abdominis, and internal and external oblique muscles, will be focused on training by the Neurac training device from the Norwegian company Redcord. Breathe evenly during training, and the training will be left for 30 min.

### 2.9. Outcome Measures

Patients will be evaluated with visual analogue scale (VAS), Oswestry Disability Index (ODI), Japanese Orthopedic Association score (JOA), gait analysis, and surface electromyography (sEMG). These indicators can help us to observe the effectiveness of the Tongdu Bushen acupuncture, intradermal acupuncture, and moxibustion integrated therapy combined with CMT in the treatment of pain and physical disorders and provide a theoretical and experimental basis for clinical application.

#### 2.9.1. Primary Index

*(1) Japanese Orthopedic Association Score (JOA)*. JOA is used to evaluate functional disorders [18]. The highest JOA score was 29, and the lowest was 0. Lower scores indicate greater dysfunction. The improvement index, the difference between posttreatment and pretreatment scores, can reflect the improvement of lumbar function before and after treatment. The clinical effect can be understood through the improvement rate (improvement rate is the ratio of posttreatment score minus pretreatment score to 29 minus pretreatment score). The improvement rate can also correspond to the commonly used therapeutic effect criteria: the improvement rate of 100% is cured, the improvement rate of more than 60% is effective, 25–60% is effective, and the improvement rate of less than 25% is ineffective.

*(2) Visual Analogue Scale (VAS)*. VAS is widely used in clinical pain assessment because of its simplicity and practicability [19]. The same method before and after clinical treatment can be used to objectively score and evaluate the effect of pain treatment. Participants looked at a walking scale and said a number between 0 (painless) and 10 (the worst pain to endure) instead of filling out a complex questionnaire. This method is simple, objective, and sensitive.

*(3) Oswestry Disability Index Score (ODI)*. ODI is often used to evaluate low back pain dysfunction [20]. The ODI scale consists of 10 parts, covering pain levels, personal care, lifting objects, walking, sitting, standing, sleep, sex life, social activities, and travel. The scores for each of the above 10 sections range from 0 to 5, with a maximum score of 50. The ODI index was obtained by dividing the patient's actual score by 50 and multiplying by 100%. The higher the ODI index, the more serious the patient's dysfunction.

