### 2.11. Statistical Analysis

All statistical analyses will be performed using SPSS Statistics for Windows Version 23.0 (IBM Corp., Armonk, NY). The normality test will be applied to all data. The *t*-test will be used if the data fit the normal distribution; otherwise, the rank sum test will be used. Counting data will be compared using the chi-square test. The significance level will be set at *P* < 0.05 and the confidence interval at 95%.

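### Sections 2.4 and 2.9.1 disagree on the primary outcome (one outcome sized on JOA, or three scales), so the stated alpha of 0.05 and power of 0.9 are jointly assured only on a reading the text does not give

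*Protocol article*

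**What the plan says.** Section 2.9.1 of the protocol article, headed "2.9.1. Primary Index", numbers three scales:

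- JOA, introduced with "JOA is used to evaluate functional disorders [18"];
- VAS, introduced with "VAS is widely used in clinical pain assessment because of its simplicity and practicability [19"];
- ODI, introduced with "ODI is often used to evaluate low back pain dysfunction [20"].

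None is called decisive. Gait analysis and sEMG have their own subsection of secondary indicators (2.9.2), so primary status was given to these three on purpose.

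Section 2.4 uses the singular: "the primary outcome was that patients' lower back pain improved". The figures that follow are JOA changes after 10 days in a pilot of 10 cases, 3.41 ± 1.86 against 2.24 ± 1.67, with alpha 0.05 and power 0.9. No effect or standard deviation is given for VAS or ODI.

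Section 2.11 gives one testing rule, "The *t*-test will be used if the data fit the normal distribution; otherwise, the rank sum test will be used", and one level: "The significance level will be set at *P* < 0.05 and the confidence interval at 95"%. Section 2.8 sets the treatment period at 3 weeks.

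**The concern.** The two sections that define the primary outcome do not agree. Section 2.4 has one outcome, calls it pain, and uses numbers from JOA. Section 2.9.1 has three outcomes, treats JOA as a function scale and VAS as the pain scale. A reader cannot tell whether the trial is decided by JOA, by VAS, or by some combination of the three.

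The introduction's hypothesis, that the experimental regimen is more effective, is tied to no scale. If one scale favours it and two do not, the text does not settle whether the trial succeeded, and the choice could be made after the results are known. The alpha and power in section 2.4 were worked out for one test, and they carry over to a three-scale decision only under particular rules.

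**Working it through.** **Inputs from the document.** Difference δ = 1.17 (3.41 − 2.24), σ = 1.86, two-sided alpha 0.05 (z = 1.96), power 0.9 (z = 1.282), 10% dropout (section 2.4); allocation 1:1 (section 2.6); three primary scales (section 2.9.1).

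**Inputs assumed.** The article gives no correlations between the three test statistics, so a common value of 0, 0.5 or 0.8 is used. It gives no effects for VAS and ODI, so where power needs them they are set equal to JOA's, 1.17/1.86 = 0.63 standard deviations.

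**1. The plan's own figure.** 2 × [(1.96 + 1.282) × 1.86/1.17]² = 2 × 5.154² = 53.13, rounded up to 54 per group. Then 54/(1 − 0.10) = 60. Both stated figures reproduce.

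**2. JOA alone decides.** Alpha is 0.05. The expected z statistic at 54 per group is √(54/2) × 0.629 = 3.269, and power is Φ(3.269 − 1.960) = Φ(1.309) = 0.905. Both stated properties hold.

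**3. Any one of three suffices, each at 0.05.** With independent tests the chance of at least one significant result when no scale differs is 1 − 0.95³ = 0.143. For correlated z statistics it was simulated with 2,000,000 draws.

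**4. All three are required.** Alpha stays at or below 0.05. With independent tests joint power is 0.905³ = 0.74. Correlated cases come from the same simulation, shifted by 3.269.

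| Assumed correlation | Any-of-three: false-positive chance | All-of-three: joint power, 54 per group |
|---|---|---|
| 0 | 14.3% | 74% |
| 0.5 | 12.5% | 79% |
| 0.8 | 9.8% | 84% |

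The any-of-three column counts significant differences in either direction. Counting only those that favour the experimental group gives 7.3%, 6.3% and 4.9%, against 2.5% for a single test.

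**5. Adjusting instead of choosing.** Bonferroni at 0.05/3 = 0.0167 leaves JOA power at 80.9% with 54 per group (normal approximation; 79.7% with the t distribution). Restoring 90% would take 69 per group, or 69/0.9 = 77 with dropout.

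**The case against.** The strongest reply is that JOA is the natural decisive scale: it is listed first and is the only one with an effect size and a sample size. On that reading alpha and power are both as stated (step 2). This stands, and it limits the point. A reader might infer that the 5% error rate is broken outright, or that one stated property must be wrong whichever rule applies. The document does not support that. It contains no rule that a win on any one scale counts as success, section 2.11 makes no claim of control across scales, and the JOA-only reading satisfies both figures. But the text does not state that reading either, and calling the outcome pain in section 2.4 points away from it.

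A second reply is that multiplicity rules and testing order are commonly left to an analysis plan, and a journal article is condensed. That also stands, so the lack of an adjustment method is not itself the point. What remains is a conflict between two sections of the article, which an analysis plan could settle only by overriding one of them.

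Third, zero correlation is implausible for overlapping scales measured in the same patients (ODI itself has a pain section), so 14.3% and 74% are the unfavourable ends of the ranges. That is fair. At a correlation of 0.8 the figures are still 9.8% and 84%.

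**Conclusion.** The point holds as an inconsistency in what is primary, with conditional consequences. The sample size calculation is arithmetically correct for one JOA comparison. The stated alpha of 0.05 and power of 0.9 are jointly assured only if JOA alone is decisive, which the article does not say. Under an any-of-three rule the false-positive chance would be about 10% to 14%. Under an all-of-three rule alpha would hold but joint power would be about 74% to 84%. Both ranges rest on assumed correlations from 0 to 0.8, and the power range also on VAS and ODI sharing JOA's standardized effect. It should be settled before any unblinded analysis, because it determines what result counts as a positive trial.

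**What to change.** Before any unblinded analysis:

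- Name one primary endpoint, in the same words, in sections 2.4 and 2.9.1, tested at two-sided 0.05. JOA change from before to after treatment is the candidate if the authors confirm that the sample size rests on it. Confirmation is needed because section 2.4 calls the outcome pain and describes the pilot changes as reductions, while section 2.9.1 says lower JOA scores are worse.
- State its time point. The sizing inputs are 10-day changes and treatment runs for 3 weeks. The two must be reconciled, since the stated power applies to the 10-day difference and spread.
- Make the other two scales key secondary endpoints, tested in a prespecified fixed order and only if the primary is significant. The order is for the authors to choose.

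With JOA confirmed as sole primary, recruitment stays at 60 per group and no alpha is divided. The cost is that VAS and ODI cannot carry a confirmatory claim if the primary fails. Section 2.5 says recruitment began in June 2021, so this is a change to a running trial and needs a dated, documented amendment and a registry update.

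If the authors want all three scales to stay primary, they should state the success rule and recompute the sample size for it, with a stated effect and standard deviation for VAS and ODI.

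### The primary JOA outcome is given in three forms with none named as primary, two response bands share one label, and the stated 90% power belongs only to the mean change

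*Protocol article*

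**What the plan says.** Section 2.9.1 lists JOA first among three primary indices, on a scale of 0 to 29 where higher is better, and expresses it in three ways:

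- the difference between the scores after and before treatment;
- an improvement rate, defined as "improvement rate is the ratio of posttreatment score minus pretreatment score to 29 minus pretreatment score";
- response bands cut from that rate. A rate of 100% counts as cured. For the rest, "the improvement rate of more than 60% is effective, 25–60% is effective, and the improvement rate of less than 25% is ineffective".

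No sentence says which of the three is the primary endpoint. Section 2.4 sizes the trial on the JOA change. Pilot treatment "can reduce scores on the JOA scale by 3.41 ± 1.86 and 2.24 ± 1.67 points, respectively", the SD and difference put into the formula "which are 1.86 and 1.17, respectively", "the test power is set to 0.9", and the result is that "54 patients will be needed in each group". Section 2.11 provides a t-test or rank sum test for measurements and adds that "Counting data will be compared using the chi-square test". It ties none of these tests to a particular form of JOA.

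**The concern.** There are two separate problems.

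**Labels.** Two bands divided by a cut-point carry the same label, *effective*. As labelled, the scale has three levels (cured, effective, ineffective) and the 60% boundary does nothing. As cut, it has four. A rate of 100% also meets the conditions of two bands. A reader of the results table could not tell which scheme was used.

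**Choice of form.** Change, rate and bands can give different answers on the same data, and all three stand under the primary heading. If none is named in advance, the choice can be made after the results are seen. The three also differ in precision, and only one of them was used to size the trial.

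The rate has a further weakness: its denominator, 29 minus baseline, shrinks as baseline rises and is zero at 29.

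**Working it through.** **1. The plan's own figure.** Inputs from Section 2.4: σ = 1.86, δ = 3.41 − 2.24 = 1.17, Z values 1.96 and 1.282. I read the pilot figures as improvements, although Section 2.4 words them as reductions and Section 2.9.1 says that lower scores are worse.

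N = 2 × [(1.96 + 1.282) × 1.86 / 1.17]² = 53.13, so 54 per group; 54 / 0.9 = 60. Both stated figures reproduce.

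Power for the mean change with 54 per arm: 1.17 / (1.86 × √(2/54)) = 3.27; 3.27 − 1.96 = 1.31; Φ(1.31) ≈ 90.5%. The stated power is met, for the change score.

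**2. A responder split at one fixed baseline.** Baseline JOA is not in the document, so the baseline here is an assumption. A patient with baseline b reaches a rate of c when the change is at least c × (29 − b). For b = 15 and c = 0.25 the threshold is 3.5 points. With the pilot means and SDs (1.86 and 1.67):

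- experimental: 1 − Φ((3.5 − 3.41)/1.86) = 48.1%
- control: 1 − Φ((3.5 − 2.24)/1.67) = 22.5%

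For two proportions with 54 per arm, the difference is 0.256 and the pooled proportion 0.353. The standard error is √(2 × 0.353 × 0.647/54) = 0.092 under the null and √((0.481 × 0.519 + 0.225 × 0.775)/54) = 0.089 under the alternative. Power is Φ((0.256 − 1.96 × 0.092)/0.089) ≈ 80%; 90% would need 72 per arm. Other baselines:

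| Assumed baseline | Power, split at 25% | Power, split at 60% |
|---|---|---|
| 8 | 59% | 3% |
| 12 | 76% | 3% |
| 15 | 80% | 6% |
| 18 | 77% | 26% |
| 20 | 72% | 56% |
| 24 | 52% | 79% |

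No split reaches 90%.

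**3. All forms compared, by simulation.** Assumptions: 54 per arm, mean changes 3.41 and 2.24, integer scores capped at 29, baseline mean 12 to 20 and SD 3 to 4, change independent of baseline.

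| Form and test | Approximate power |
|---|---|
| Change, t-test | 86–92% |
| Improvement rate, t-test | 64–87% |
| Bands cut at 25%, 60% and 100%, general chi-square | 45–65% |
| Same bands in order, rank test | 55–73% |

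The end score adjusted for baseline matched the change here, and reached 93–96% when change was correlated −0.4 with baseline. Under such a correlation the rate and the bands also gain power, and at low baselines the rate can come level with the change.

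**4. The ratio near the ceiling.** A 2-point loss from 27 gives (25 − 27)/(29 − 27) = −100%. The same loss from 10 gives (8 − 10)/(29 − 10) = −10.5%. At baseline 29 the denominator is zero and there is no rate.

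**The case against.** A reader might infer that the response outcome is wrong and that the trial is far less powerful than planned. The protocol supports neither.

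- No power was planned for a response outcome. The 90% was planned for mean change, and it is met.
- The bands are introduced as a further reading of the rate, not as the primary test. The chi-square sentence in Section 2.11 covers all count data and is not tied to JOA.
- The 25% and 60% cut-points are numerically distinct. The repeated label may be a slip of wording, and a split at 25% is unaffected by it. Read from the top, with cured first, the overlap at 100% also resolves.
- The size of the power loss depends on a baseline that the document does not report. Section 2.11 would also send a skewed rate to the rank sum test.
- Baselines near 29 should be few among symptomatic patients. Under the assumed distributions the share at 27 or above is below 2%, except with mean 20 and SD 4, where it is about 5%. The −100% and −10.5% in the example both fall in the ineffective band, so they distort an average rate but not the bands.

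All of this stands, and it limits the point to what follows. It does not remove the duplicate label, which is printed in the text, or the missing choice among three forms under a primary heading. A fuller plan may hold derivation details, but this text leaves the choice open.

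**Conclusion.** The point holds as a matter of definition. JOA has three forms under the primary heading and none is named, the bands are labelled so that the 60% cut-point has no effect, and a 100% rate belongs to two bands. The 90% power covers the mean change alone (1.17 points, SD 1.86, 54 per group).

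For the other forms, 54 per arm give roughly 64–87% (rate, t-test) and 45–65% (bands, general chi-square). These ranges rest on assumed baseline means of 12 to 20 and SDs of 3 to 4, with change independent of baseline. They would be higher if patients with low baselines improved more. They show what would be lost if the rate or the bands were used as the primary result; they are not a shortfall in the planned analysis. The instability of the rate near 29 is real arithmetic, but it matters only if patients with high scores enrol.

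**What to change.** In Section 2.9.1:

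1. Name one primary form of JOA: the end-of-treatment score adjusted for baseline, or the change as sized in Section 2.4.
2. Make the improvement rate and the bands secondary.
3. Give each band its own label and make the bands exclusive, for example 100%, above 60% but below 100%, 25–60%, and below 25%.
4. State that the rate is undefined at baseline 29.

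In Section 2.11, compare the ordered bands with a trend or rank test in place of the general chi-square. Under the assumptions above this raises power from about 45–65% to about 55–73%.

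The change costs wording only and leaves the sample size as it is. The downside is that the responder table can no longer be presented as a primary claim.
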